### 2.9. Sample size and recruitment assumptions

DREAMER uses a pragmatic recruitment target based on expected RSWA frequency and feasibility within participating centers. Previous quantitative work in adults without RBD showed that isolated RSWA elevations may be detected in a substantial minority of individuals, with approximately 14% of patients without dream-enactment behavior reaching previously established RBD-level RSWA thresholds [4,7]. Therefore, the initial recruitment target is > 500 participants over 18 months, expected to yield approximately 85 individuals with isolated RSWA. Because the DREAMER population is restricted to adults aged ≥40 years, and because RSWA becomes more frequent with age, the number of isolated RSWA cases may exceed this estimate.

The initial 24-month phase is not designed as a definitive phenoconversion trial. Instead, it is designed to assemble an enriched cohort and collect the standardized baseline data required for adequately powered follow-up. Recruitment assumptions will be reassessed after the first 6 months of enrollment. If the observed frequency of isolated RSWA or the rate of technically classifiable vPSG recordings is lower than expected, recruitment targets may be increased, and the comparator strategy may be adjusted by selecting an age- and sex-matched subgroup without RSWA for long-term follow-up.

Assuming approximately 85 participants with isolated RSWA and long-term follow-up over 5 years, the study may observe a sufficient number of incident RBD events to generate preliminary estimates of relative risk compared with participants without RSWA. These estimates will be used to plan future prevention or neuroprotection trials rather than to support immediate clinical implementation.

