### 2.11. Statistical analysis plan

Baseline characteristics will be summarized for the overall cohort and stratified by RSWA status. Continuous variables will be reported as mean and standard deviation or median and interquartile range, according to distribution. Categorical variables will be reported as counts and percentages.

Participants with isolated RSWA will be compared with participants without RSWA. Continuous variables will be analyzed using Student’s t test or Mann-Whitney U test, as appropriate. Categorical variables will be analyzed using chi-square or Fisher’s exact tests. Effect sizes and confidence intervals will be reported whenever possible to avoid overreliance on significance testing.

RAI will be analyzed both as a continuous variable and as a categorical classification variable. Multiple linear regression will evaluate associations between RAI and clinical, pharmacological, sleep, and neurophysiological predictors. Logistic regression will evaluate predictors of isolated RSWA status. Candidate covariates will include age, sex, antidepressant exposure, neurological comorbidity, sleep apnea severity, REM sleep duration, and participating center.

For long-term follow-up, cumulative incidence of RBD will be described using Kaplan-Meier methods. Cox proportional hazards models will estimate the association between baseline isolated RSWA and incident RBD, adjusted for age, sex, medication exposure, center, and relevant sleep-disorder comorbidities. Competing-risk methods may be considered for incident neurodegenerative outcomes or death. Sensitivity analyses will evaluate the influence of antidepressant exposure, minimum REM duration, comorbid sleep apnea, and alternative RAI thresholds.

The extent and pattern of missing data will be reported. If missingness is limited, complete-case analyses will be used. If missingness is substantial and plausibly missing at random, multiple imputation may be considered for regression models. Follow-up attrition will be summarized and compared between RSWA and non-RSWA groups.

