### 2.12. Study status and timeline

The DREAMER study was registered at ClinicalTrials.gov before completion of recruitment. Ethics approval was obtained on 24 January 2024, and participant recruitment started on 22 February 2024. At the time of submission of this Study Protocol, participant recruitment is still ongoing and has not yet been completed, although the recruitment phase is close to completion. Recruitment is expected to be completed by 30 June 2026.

Completion of participant recruitment will be followed by baseline data verification, RAI computation, classification of participants according to the predefined RSWA/RAI criteria, identification of the isolated RSWA subgroup, and selection of the comparator group without RSWA according to the prespecified matching strategy. Therefore, the analytical cohort has not yet been constituted, and no study results have yet been generated, analyzed, or reported.

After completion of recruitment, baseline data validation, and analytical cohort constitution, the longitudinal follow-up phase will begin and will continue for 5 years. Follow-up data collection is expected to be completed approximately by 30 June 2031. Baseline descriptive and feasibility results are expected only after completion of recruitment, database verification, RAI-based classification, comparator-group selection, and database lock, approximately by September–December 2026. Final longitudinal analyses of incident REM sleep behavior disorder and neurodegenerative outcomes are expected after completion of the planned 5-year follow-up period, approximately by late 2031 or early 2032.

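### The incident-RBD hazard ratio is set as an ordinary, fully adjusted Cox model without stated event rates or comparator size; with few events it would be fragile, and with a small matched comparator it may be infinite

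*Protocol article*

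**What the plan says.** Section 2.9 sizes the exposed group only. It cites "approximately 14% of patients without dream-enactment behavior reaching previously established RBD-level RSWA thresholds" and concludes that "the initial recruitment target is > 500 participants over 18 months, expected to yield approximately 85 individuals with isolated RSWA". For the longitudinal question, its starting point is "Assuming approximately 85 participants with isolated RSWA and long-term follow-up over 5 years". On that basis it expects that "the study may observe a sufficient number of incident RBD events to generate preliminary estimates of relative risk compared with participants without RSWA". The purpose is stated next: "These estimates will be used to plan future prevention or neuroprotection trials rather than to support immediate clinical implementation". The section gives no RBD incidence, loss rate, target hazard ratio or precision.

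The comparator size is left open. Section 2.9 offers matching as a contingency: "the comparator strategy may be adjusted by selecting an age- and sex-matched subgroup without RSWA for long-term follow-up". Section 2.12 describes it as the plan: "selection of the comparator group without RSWA according to the prespecified matching strategy". Neither gives a ratio.

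Section 2.11 describes cumulative RBD incidence by Kaplan-Meier and then fixes the regression: "Cox proportional hazards models will estimate the association between baseline isolated RSWA and incident RBD, adjusted for age, sex, medication exposure, center". The adjustment list also takes in comorbid sleep disorders judged relevant. It attaches no event-count condition and names no penalized or reduced alternative.

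**The concern.** The precision of a relative risk is governed mainly by the group with fewer events. The 14% in section 2.9 is a frequency of RSWA, not an incidence of RBD, so nothing in that section bears on how many events either group will produce.

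Maximum partial likelihood behaves badly with few events. If one group has none, its hazard ratio has no finite estimate and the Wald interval is meaningless. The same happens to an indicator for a center without events. Short of that, an estimate resting on one or two events per coefficient is biased away from the null and very imprecise.

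Incident RBD is the primary long-term clinical outcome (section 2.7), and this hazard ratio is meant to inform the design of later trials. An infinite or hundredfold-wide estimate would not serve that purpose.

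**Working it through.** **The plan's own figure.** 500 × 0.14 = 70, not 85. Reaching 85 needs 85 / 0.14 ≈ 607 enrolled, or a frequency of 85 / 500 = 17%. The target is open-ended (above 500), so 85 is attainable. The statement about events has no inputs and cannot be reproduced.

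**Coefficients.** RSWA 1, age 1, sex 1, medication at least 1, center 3 (four centers, as indicators), sleep comorbidity at least 1: at least 8.

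**Assumptions (not in the documents).** RBD hazard *h* of 2% to 4% per year with isolated RSWA and 0.2% to 1% per year in comparators; loss *d* = 5% per year; 5 years. The comparator number is 85 (1:1 matching) or 415 (500 − 85, everyone else).

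**Expected events.** The probability of an observed event is p = h/(h+d) × [1 − exp(−5(h+d))].

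| h per year | p | events in 85 | events in 415 |
|---|---|---|---|
| 0.2% | 0.0088 | 0.75 | 3.7 |
| 0.5% | 0.0219 | 1.9 | 9.1 |
| 1% | 0.0432 | 3.7 | 17.9 |
| 2% | 0.0844 | 7.2 | – |
| 4% | 0.1611 | 13.7 | – |

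The lowest total is 7.2 + 0.75 ≈ 8 events (2% vs 0.2%, 85 vs 85), or 8/8 = 1 per coefficient. The highest is 13.7 + 17.9 ≈ 32 (4% vs 1%, 85 vs 415), or 32/8 = 4 per coefficient.

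**Chance of no comparator event, hence an infinite RSWA hazard ratio: (1 − p)^n.**
- n = 85: 47% at 0.2% per year, 15% at 0.5%, 2% at 1%.
- n = 415: 2.5% at 0.2% per year, about 0% at 0.5% and above.

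Simulating the 8-coefficient Cox model gave matching shares of infinite RSWA hazard ratios: 46% (2% vs 0.2%) and 15% (4% vs 0.5%) at 85 vs 85, and 3% and 0% at 85 vs 415. A separate run at 85 vs 415 gave 4% and 0%.

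**Imprecision when finite.** Another simulation used 5-year risks, with RSWA risk at 10% to 30% and 150 runs per cell. A 5-year risk of 1% corresponds to about 0.2% per year. The share of runs with an infinite RSWA hazard ratio or a 95% interval wider than 50-fold (upper/lower limit) was:

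| comparator 5-year risk | 85 comparators | 415 comparators |
|---|---|---|
| 0.5% | 94–96% | 46–51% |
| 1% | 79–85% | 12–15% |
| 2% | 51–64% | 0–1% |

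**Other terms.** With 415 comparators and RSWA risk 10%, some coefficient diverged beyond ±8 in 36%, 28% and 13% of runs at comparator risks of 0.5%, 1% and 2%. At RSWA risk 20% the shares fell to 5%, 5% and 2%.

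**The case against.** A reader might infer that comparator events will be close to zero and that the hazard ratio will therefore often be infinite, whatever comparator is chosen. The documents do not support that.

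- No document figure gives a comparator rate. Comparators are those not below RAI 0.85, so they include 0.85 to 0.9, which section 2.5 classes as mildly abnormal. Section 2.4 also concedes that dream enactment may be under-recognized at baseline. Both could raise the comparator rate.
- No passage states 85 comparators. Matching is a contingency in section 2.9, section 2.12 gives no ratio, and Table 2 lists annual follow-up as planned for all enrolled participants. With about 415 comparators an infinite RSWA hazard ratio is uncommon. A diverging center or covariate term does not by itself make the RSWA term infinite.
- Adjustment for center does not have to mean indicators, so eight coefficients is an inference.
- Section 2.9 is hedged: the estimates are preliminary and claim no power. Section 2.11 already plans Kaplan-Meier incidence, so the question does not rest on the hazard ratio alone.
- Estimation detail of this kind is often left to an analysis plan.

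The first four bullets stand and limit the point. The last carries less weight here, because the article itself names the model, lists the covariates and states the conclusion about events. The concern is with what is stated, not with what is left out.

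**Conclusion.** The point holds in limited form. The sufficiency statement in section 2.9 has no event rates or comparator size behind it, and section 2.11 commits to an ordinary adjusted Cox model regardless of events. Under the assumed rates this gives about 1 to 4 events per coefficient.

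How serious this is depends on the comparator. With 1:1 matching and 0.2% to 0.5% per year, the RSWA hazard ratio is infinite in roughly 15% to 50% of realizations and often very imprecise otherwise. With about 415 comparators, infinity occurs in 0% to 4%, and what remains is width and diverging nuisance terms at the lowest rates. From a 2% five-year comparator risk upward, the large-comparator analysis is largely stable unless the RSWA rate is itself low.

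This is an unsupported feasibility statement joined to a model that is not robust to sparse events. It is not a wrong power calculation. The change is worth making because it is cheap and, as section 2.12 says that no results exist, cannot be data-driven.

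**What to change.** In section 2.11, estimate the incident-RBD hazard ratio with a Firth-penalized Cox model and profile-likelihood intervals, and handle center by stratification. Keep the listed confounders, or carry them in one propensity score if events are few. Report the planned Kaplan-Meier 5-year incidence in each group, with intervals, beside the hazard ratio. In the scenarios simulated, the penalized estimate stayed finite and close to the true value, and it nearly matched ordinary Cox when events were ample.

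In section 2.9, replace the sufficiency statement with expected events per group over a stated range of rates and comparator sizes, and the interval width that follows. State the comparator size or matching ratio there, consistent with section 2.12.

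The cost is wording and standard software, with no extra participants. The downside is slight shrinkage of the hazard ratio and a less favorable statement of precision.

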### 2.12. Study status and timeline

The DREAMER study was registered at ClinicalTrials.gov before completion of recruitment. Ethics approval was obtained on 24 January 2024, and participant recruitment started on 22 February 2024. At the time of submission of this Study Protocol, participant recruitment is still ongoing and has not yet been completed, although the recruitment phase is close to completion. Recruitment is expected to be completed by 30 June 2026.

Completion of participant recruitment will be followed by baseline data verification, RAI computation, classification of participants according to the predefined RSWA/RAI criteria, identification of the isolated RSWA subgroup, and selection of the comparator group without RSWA according to the prespecified matching strategy. Therefore, the analytical cohort has not yet been constituted, and no study results have yet been generated, analyzed, or reported.

After completion of recruitment, baseline data validation, and analytical cohort constitution, the longitudinal follow-up phase will begin and will continue for 5 years. Follow-up data collection is expected to be completed approximately by 30 June 2031. Baseline descriptive and feasibility results are expected only after completion of recruitment, database verification, RAI-based classification, comparator-group selection, and database lock, approximately by September–December 2026. Final longitudinal analyses of incident REM sleep behavior disorder and neurodegenerative outcomes are expected after completion of the planned 5-year follow-up period, approximately by late 2031 or early 2032.

### 2.13. Ethical and regulatory considerations

DREAMER will be conducted in accordance with the Declaration of Helsinki, applicable national regulations, and institutional ethics requirements. The study protocol was approved by the Comitato Etico Locale IRCCS Oasi Maria SS on 24 January 2024 (approval number CEL-IRCCS OASI/24-01-2024/EM02). Written informed consent will be obtained from all participants before inclusion. Because the study is observational and non-interventional, risks are primarily related to confidentiality, routine video-polysomnography burden, ancillary neurophysiological procedures, and blood sampling. Participants will receive standard clinical management for any clinically relevant findings emerging from routine care. The study was registered at ClinicalTrials.gov as DREAMER – IsolateD REM Sleep Without Atonia as a Risk Factor for REM Sleep Behavior disordER (ClinicalTrials.gov Identifier: NCT06140511; Unique Protocol ID: PNRR MR1 2022–12375694).

## 3. Discussion

DREAMER addresses a critical methodological barrier in the development of prevention trials for synucleinopathies: the need to identify and characterize individuals at risk before overt RBD or neurodegenerative disease develops. Isolated RBD is already a strong marker of future alpha-synucleinopathy, but it may be too late in the prodromal sequence for some preventive strategies. Isolated RSWA is biologically plausible as an earlier stage, because RSWA is the PSG substrate of RBD and may appear before clinically evident dream enactment; however, available longitudinal data remain limited and partly divergent [10–12]. However, isolated RSWA cannot yet be used as a trial-enrichment marker without prospective evidence, harmonized measurement, and reproducible cohort infrastructure.

The design of DREAMER is therefore deliberately trial-oriented, despite its observational nature. It incorporates several features relevant to future clinical trials: a prespecified eligibility framework, standardized vPSG-based classification, quantitative automated RSWA measurement, centralized eCRF architecture, predefined data-quality checks, multicenter recruitment, collection of confounders, and ancillary biomarker assessments. These elements will facilitate later conversion of the cohort into a risk-enriched platform for observational follow-up, nested case-control analyses, and potentially future preventive or disease-modifying trials.

The use of RAI is a central methodological feature. Manual RSWA scoring is informative but may be time-consuming and variable across laboratories. A quantitative automated index provides a scalable approach that can be applied across centers [14–16,29] and may support reproducible risk classification. The selected threshold of RAI < 0.85 is intended to enrich the cohort for abnormal REM atonia loss while retaining sufficient sensitivity for a prospective risk-identification study; sensitivity analyses using more stringent thresholds, including RAI < 0.8, will be important.

DREAMER also incorporates multimodal neurophysiology. TMS may identify cortical excitability changes related to inhibitory and facilitatory circuits. VEMPs and BAEPs may capture brainstem dysfunction relevant to REM atonia regulation. Blood-based omics may reveal peripheral signatures overlapping with those previously reported in isolated RBD. Although these ancillary assessments are exploratory, they may help determine whether isolated RSWA is merely a polysomnographic finding or part of a broader prodromal neurobiological profile.

Several limitations should be acknowledged. First, DREAMER recruits from sleep-center populations rather than the general population; therefore, RSWA frequency estimates may not be population prevalence estimates. Second, isolated RSWA may be heterogeneous, reflecting age, sex, antidepressant or psychoactive medication exposure, psychiatric status, sleep fragmentation, respiratory events, neurological comorbidities, observer availability, or subclinical RBD [5,7–9,12]. Because sleep-disordered breathing may complicate RSWA interpretation, sensitivity analyses stratified by sleep apnea severity and respiratory-event-related arousals will be important [30]. The protocol addresses this through systematic collection of confounders and sensitivity analyses, but residual confounding is likely. Third, the 24-month funded phase is primarily a cohort-construction period and cannot by itself provide definitive phenoconversion evidence. Fourth, long-term follow-up requires sustained funding, participant retention, and harmonized outcome adjudication. Finally, RBD diagnosis during follow-up may depend on repeat vPSG availability, which may vary across centers and over time.

Despite these limitations, DREAMER is positioned to make a methodological contribution. Contemporary trial development in neurodegeneration increasingly depends on earlier risk detection, biomarker enrichment, scalable data infrastructure, and harmonized multicenter operations. DREAMER provides a framework for moving isolated RSWA from an incidental PSG observation toward a systematically characterized risk state that can be evaluated for future clinical trial enrichment.

## 4. Conclusions

DREAMER is a multicenter, prospective, registry-like cohort designed to identify isolated RSWA in adults without RBD using harmonized vPSG and quantitative RAI assessment. By integrating standardized clinical assessment, secure eCRF-based data capture, neurophysiological testing, biobanking, and planned long-term follow-up, DREAMER aims to build trial-ready infrastructure for evaluating isolated RSWA as an early risk marker in the RBD-synucleinopathy continuum. If isolated RSWA proves to predict incident RBD, this framework may support earlier enrollment windows for future preventive and neuroprotective trials.
